## Abstract

**Background:**

The prevalence of dementia is increasing in Canada and in many countries internationally. People living with dementia are highly dependent on family and friend care partners, who may have little knowledge of the disorder. Web-based interventions in dementia have been shown to improve care partner mental health and reduce burden, but few have been widely implemented or rigorously studied. We developed a web- and email-based dementia education platform for care partners, iGeriCare, which includes 12 asynchronous, multimedia, e-learning lessons and email-based content to reinforce the learning.

**Objective:**

The primary objective of this pilot study is to evaluate the feasibility and care partner acceptance of the intervention, including study methods. Secondary objectives will examine the effectiveness of the educational resources on family care partners’ knowledge, self-efficacy, and sense of burden.

**Methods:**

This study is a 2-arm, pilot, feasibility, randomized controlled trial. A total of 125 family or friend care partners for a person living with dementia—who are residing in Canada, aged 16+ years, and comfortable using the internet and email—will be recruited using coinvestigator networks and Facebook digital marketing advertisements. Participants will be randomly assigned to either the intervention group (receiving the dementia web- and email-based educational intervention) or the control group (receiving an alternate topic e-learning lesson and emails) and will have 8 weeks to complete baseline surveys and the assigned e-learning. After 8 weeks, participants will have 2 weeks to complete poststudy surveys. This protocol will be repeated with a second cohort of 100 care partners recruited from a paid panel service based on learnings from initial feasibility results.

**Results:**

Initial recruitment began on September 6, 2022, and concluded on October 2, 2022. A total of 125 participants were randomly assigned to the intervention (n=61) or control (n=64) group. Data collection concluded in January 2023. Preliminary feasibility results showed a substantial number of participants who did not engage with the protocol as intended. A decision was made to recruit a second cohort of participants to address these protocol deviations. Secondary recruitment began on June 12, 2023, and concluded on June 27, 2023. A total of 100 participants were randomly assigned to the intervention (n=53) or control (n=47) group. Data collection concluded in September 2023. Further results will be published in peer-reviewed journals and presented at conferences.

**Conclusions:**

This study is investigating the feasibility, acceptability, and effectiveness of a web- and email-based dementia care partner educational intervention. The results of this study will contribute to the planning of a larger randomized controlled trial in the future, as well as the evaluation of innovative, cost-effective, and efficient dementia care partner resources that can complement traditional approaches.

**Trial Registration:**

ClinicalTrials.gov NCT05114187; https://clinicaltrials.gov/study/NCT05114187

**International Registered Report Identifier (IRRID):**

DERR1-10.2196/67048

## Introduction

### Dementia Care Partners

People living with dementia rely on family care partners to provide support, most often without any formal dementia education. In Canada, at least 486,000 people identify as caring for an individual with dementia [1]; many more constitute informal family or friend care partners. By 2025, Canada will have more than 1 million care partners for people living with dementia who will provide an estimated 1.4 billion hours of care annually [1-5].

Numerous quality standards highlight the importance of education that helps care partners develop knowledge and skills to support themselves and a person with dementia in living well [1,6-8]. Providing evidence-based education to help care partners better understand dementia, its progression, treatment options, and available supports can be challenging to do in the clinical setting; time and resource constraints can impede a provider’s ability to provide education. Although several education programs currently exist, they vary in availability and often lack the flexibility to accommodate the realities of caregiving.

### Web-Based Strategies

Care partner–focused, web-based interventions have been shown to be both feasible and effective with respect to a range of outcomes. Recent systematic reviews found evidence for the positive effects of web-based interventions on self-efficacy, self-esteem, and strain of care partners of adults living with a chronic condition [9-13]. There is also evidence for the benefit of internet-based interventions on mental health for care partners of adults living with a chronic condition, particularly for the outcomes of care partner depression, stress and distress, and anxiety [14].

However, there remains a shortage of freely available, asynchronous, web-based programs that incorporate principles of multimedia learning design. Care partners of people diagnosed with dementia have identified the need for high-quality, accessible, and trusted internet resources [15]. There are several frequently unmet needs in dementia care partner education including flexible delivery methods as well as rigorous evaluation of program effectiveness [16-18]. Existing programs often rely on real-time components such as synchronous (live) webinars, which can be inconvenient for care partners and challenging to scale and spread. A recent scoping review highlighted the importance of several components of internet interventions, including evidence-based instructional design, codesigning online education with care partners and experts in dementia care, and using randomized controlled trials (RCTs) to more rigorously evaluate their effectiveness [19]. Comparable web-based educational programs in other chronic disease contexts provide valuable insights. The RHAPSODY program for young-onset dementia caregivers showed significant improvements in care partner confidence but required scheduled participation [20]. The STAR portal for dementia care partners demonstrated knowledge gains but faced challenges with user engagement and retention [21]. These experiences highlight the importance of flexible, asynchronous delivery and robust instructional design.

### iGeriCare: Web-Based Educational Program for Dementia Caregivers

iGeriCare is a free, evidence-based, web- and email-based educational program for family and friend care partners of people living with dementia. It was developed by experts in dementia, e-learning, mental health, and lived experience caregiving to help meet the needs of care partners by improving their knowledge, and to raise awareness of strategies and services to improve their self-efficacy and quality of life [22-24].

iGeriCare is unique when compared to other care partner educational resources because it is one of the few web-based dementia care partner interventions to incorporate best practices in multimedia e-learning instructional design, asynchronous lessons, and email-based microlearning while remaining open access (free of cost) and without requiring users to create an account or log-in. Key components of the instructional design include the use of the principles of multimedia learning and audio narration; personalization, including the use of a visual “coach” or embodied instructional agent; segmenting the content into manageable topics to reduce cognitive load; authentic scenarios and worked examples; interactive review questions; and learner control over navigation [22]. An iterative, participatory instructional design and development methodology, the Successive Approximation Method [23], was used, with extensive involvement and review from a range of experts in dementia care, including lived-experience dementia care partners.

The asynchronous and fully web-based elements of the intervention have proven even more valuable during the COVID-19 pandemic when many face-to-face approaches have been unavailable [24]. It is easy to implement for clinicians and is an efficient and cost-effective way to address dementia care quality standards. This study, which is the first clinical trial studying the feasibility and effectiveness of the iGeriCare platform in a clinical trial, will be an important contribution to the literature on care partner web-based interventions. These innovations are an important complement to traditional approaches to care partner education, a key component of quality dementia care.

### Research Aim

The overall aim of this study is to explore the feasibility, acceptability, and effectiveness of iGeriCare, a web- and email-based dementia care partner educational intervention.

### Specific Objectives

The specific objectives of this study are to evaluate the feasibility and care partner acceptance of the intervention and other study methods and to examine the effectiveness of the educational resources on family care partners’ knowledge, self-efficacy, and sense of burden.

### Research Questions

This study aims to answer the following research questions: (1) Is the intervention feasible for participants? (2) Are participants engaged and satisfied with iGeriCare? (3) Does iGeriCare increase knowledge of dementia? (4) Does iGeriCare increase self-efficacy? and (5) Does iGeriCare decrease burden?

## Methods

### Study Design

This study is a 2-arm, pilot, feasibility RCT with intervention and control groups. Participants will receive assessments at baseline (T1) and 8 weeks (T2).

### Research Platform, Learning Management System, and Email Campaign

Developers in the Division of e-Learning Innovation at McMaster University created a web-based research platform capable of hosting participant eligibility screening, informed consent, and block randomization. Microlearning email campaigns were set up in the MailChimp email marketing and automation platform, with a campaign to schedule 2 emails per week to each participant to reinforce the learnings from either the intervention or control e-learning. A total of 2 courses (intervention and control) were set up in the Litmos learning management system to host the prestudy surveys, e-learning lessons, and poststudy surveys for each group.

### Participants

#### Inclusion and Exclusion Criteria

Individuals who meet the following self-reported inclusion criteria will be invited to participate in the study: (1) family or friend care partner of a person living with dementia, (2) reside in Canada, (3) 16+ years of age, (4) able to read and listen to English, (5) access to email and internet, and (6) comfortable using email and internet. Participants who answer “yes” to all 6 questions using the research platform will be invited to read the study information and provide informed consent before creating a participant account.

#### Sample Size

A total of 125 participants will be recruited in anticipation of a dropout rate of up to 30%, based on retention rates from previous trials on web-based interventions for our target population [10,25-27]. We expect a final sample size of 80 (n=40 per group), which will be sufficient to assess the feasibility and acceptability of the intervention.

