#### Randomization and Intervention Assignment

Following account creation, the research platform will automatically randomly assign participants either to the intervention group or the control group using stratified permuted block randomization with variable block sizes of 4, 6, and 8 (randomly arranged) in a ratio of 1:1, based on care partner type (care partner to a spouse, care partner to a parent, and care partner to someone other than a spouse or parent), and level of education (high school equivalent or less, some college or university, and college or university or graduate degree).

Once a participant is randomly assigned to either the intervention or control group, an application programming interface (API) will be used to assign each participant to the matching microlearning email campaign and course in the learning management system. Participants will receive an account verification email and once verified can begin to access their assigned surveys and web-based course (prestudy surveys, e-learning lesson[s], and poststudy surveys).

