**Figure 2 figure2:**
[figure not shown]
Study flow diagram for run 1.

Preliminary results showed a substantial number of participants who did not engage with the protocol as initially intended. A number of participants were identified as not having completed the protocol as intended, as demonstrated by “fast-tracking” through the e-learning (ie, clicking next without allowing time for reading or listening to content) or by repeatedly clicking “I don’t know” on prestudy or poststudy surveys.

Following this, a decision was made to recruit an additional cohort of participants (n=100) using learnings gained from the initial recruitment cohort concerns. A paid panel service, AskingCanadians, was engaged to assist with recruitment. AskingCanadians is a reputable paid panel service that was able to specifically target family and friend care partners of people living with dementia.

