### Future Results

Results from run 2 of the RCT will be analyzed in spring 2025, published in peer-reviewed journals in the field of aging and geriatrics, and presented at relevant conferences in fall 2025. Results will report on the overall feasibility of implementation of iGeriCare e-learning components in a clinical trial context; care partner acceptance of the intervention (including study methods and participant process); as well as any changes in knowledge, self-efficacy, and burden.

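### The Sample Size figures do not agree: 125 recruits with at most 30% dropout leave at least 87 to 88, whereas the stated final 80 implies 36% dropout

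*Protocol article*

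**What the plan says.** The Sample Size section gives three numbers for the initial cohort. The recruitment target and the dropout allowance come together: "A total of 125 participants will be recruited in anticipation of a dropout rate of up to 30" percent, with earlier web-based trials cited as the basis for the rate. The expected result follows: "We expect a final sample size of 80 (n=40 per group), which will be sufficient to assess the feasibility and acceptability of the intervention". Allocation is "in a ratio of 1:1" (Randomization and Intervention Assignment), so the 80 divides evenly.

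The Methods part of the Abstract adds a second run: "This protocol will be repeated with a second cohort of 100 care partners recruited from a paid panel service". The Results section reports 61 and 64 randomised in run 1 and 53 and 47 in run 2. The article states no dropout rate and no final target specific to run 2.

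**The concern.** A sample-size statement for a feasibility trial should let a reader go from the number recruited, through the assumed loss, to the number expected at the end. Here that calculation does not return the stated result. One of the three figures must be wrong, or a further loss was assumed and not stated.

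The practical stake is modest. The article says the results will help to plan a larger trial, and an assumed retention rate is one of the inputs such planning uses. As written, a planner could take either 30% (stated) or 36% (implied) as the loss this pilot allowed for. There is also a question of scope: the judgement that 80 is enough was written for a cohort of 125, and the protocol was then repeated with 100.

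**Working it through.** **Inputs**

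- Recruited, run 1: N = 125 (Sample Size).
- Dropout: d of at most 0.30 (Sample Size).
- Stated final sample: 80, or 40 per group (Sample Size).
- Allocation: 1:1 (Randomization and Intervention Assignment).
- Run 2: 100 randomised, 53 and 47 (Second Cohort Participants).

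**Step 1. Try to reproduce the stated 80.** Retained = N × (1 − d) = 125 × 0.70 = 87.5, that is 87 or 88 in total and 43.75 per group. Because 30% is an upper limit, this is the smallest number consistent with the text. It exceeds 80 by 7.5, which is 7.5/80 = 9.4% and too much for rounding. The stated figure is not reproduced.

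**Step 2. Find the dropout that gives 80.** d = 1 − 80/125 = 0.36. At 35%, 125 × 0.65 = 81.25. So 80 corresponds to a loss of about 35% to 36%, beyond the ceiling.

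**Step 3. Work backwards from 80 at 30%.**

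| Method | Calculation | Recruits needed |
|---|---|---|
| Divide the total by retention | 80/0.70 = 114.3 | 115 |
| Divide per group and round up | 40/0.70 = 57.1, so 58 × 2 | 116 |
| Multiply up by the dropout rate (a common mistake) | 80 × 1.30 | 104 |

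None of these gives 125.

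**Step 4. Run 2, on the assumption that the same ceiling applies.** 100 × 0.70 = 70. By arm, 53 × 0.70 = 37.1 and 47 × 0.70 = 32.9, so both arms fall below 40. To keep 80 of 100, dropout must be at most 1 − 80/100 = 20%.

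| Assumed dropout in run 2 | Retained of 100 |
|---|---|
| 10% | 90 |
| 20% | 80 |
| 25% | 75 |
| 30% | 70 |

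**The case against.** The strongest reply is that nothing in run 1 is harmed. At the worst dropout foreseen, 87 or 88 participants remain, more than the 80 said to be enough, and Conclusions and Next Steps says that the study was not powered to assess effectiveness fully. That stands, and it is why the point is minor. It does not make the three numbers agree.

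A second reply is that the authors may have allowed for a further loss between consent, account creation and randomisation. Going from 87.5 to 80 would take an extra 1 − 80/87.5 = 8.6%. The text mentions no such allowance, and all 125 are reported as randomised, so this cannot be relied on.

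On run 2 the reply has more force. The 125, the 30% and the 80 were written for the initial cohort. Run 2 came from a paid panel, chosen because of poor engagement in run 1, so its dropout could differ. That the article gives run 2 no size rationale of its own is not a fault in a condensed report.

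A reader might also infer three stronger points that the article does not support:

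- **That run 2 alone supplies the results.** Future Results says "Results from run 2 of the RCT will be analyzed in spring 2025", but this gives timing only. Data Analysis covers both cohorts.
- **That attrition will be judged against 30%.** Feasibility of the Study Methods lists completion and attrition rates and sets no such benchmark.
- **That precision is lost for attrition itself.** Attrition proportions take randomised participants as the denominator, and both run 2 arms (53 and 47) exceed 40.

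**Conclusion.** The inconsistency in the Sample Size section is certain and rests only on figures printed there: at least 87 to 88 retained against a stated 80, or equivalently 36% implied dropout against a stated maximum of 30%. No usual calculation reconciles them. Its severity is minor, because run 1 over-covers its target and no stated power depends on the 80.

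The run 2 statement is conditional. It is tempting to say that run 2 falls short of the plan's final sample. The article does not establish this, because it gives no dropout rate or target for that cohort. What can be said is that the only rate given, applied to a protocol described as repeated, leaves about 70 (about 37 and 33), and that the 80 called sufficient is reached only if dropout is 20% or less. The sufficiency statement therefore cannot be carried over to run 2 unexamined. The shortfall would be against that statement, not against any power calculation.

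**What to change.** Restate the Sample Size section in one of two ways, whichever matches what was intended:

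- *125 participants allow for up to 36% dropout while retaining 80 (40 per group)*; or
- *125 participants with up to 30% dropout retain at least about 87 (43 to 44 per group)*.

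Then either limit the sufficiency statement to run 1, or restate it for run 2 with its own figure: 100 randomised retain about 70 if dropout is 30%, and 80 if it is 20%.

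The cost is a few sentences. No extra enrolment, design change or change of analysis is involved. If run 2 is restated at 30%, its expected final number will look less favourable than 80.

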#### Recruitment

Facebook digital marketing advertisements will be used to recruit potential participants on a rolling basis until 125 eligible participants provide informed consent. Facebook has been found to be an increasingly effective and low-cost tool to drive the digital recruitment of research study participants [28]. Using targeted audience demographic selection, only persons who have been predetermined by Facebook to have “interest” in relevant topics (ie, Alzheimer disease, dementia, and caregiving) will receive study advertisements.

#### Randomization and Intervention Assignment

Following account creation, the research platform will automatically randomly assign participants either to the intervention group or the control group using stratified permuted block randomization with variable block sizes of 4, 6, and 8 (randomly arranged) in a ratio of 1:1, based on care partner type (care partner to a spouse, care partner to a parent, and care partner to someone other than a spouse or parent), and level of education (high school equivalent or less, some college or university, and college or university or graduate degree).

Once a participant is randomly assigned to either the intervention or control group, an application programming interface (API) will be used to assign each participant to the matching microlearning email campaign and course in the learning management system. Participants will receive an account verification email and once verified can begin to access their assigned surveys and web-based course (prestudy surveys, e-learning lesson[s], and poststudy surveys).

#### Participant Support

Participants will be invited to email the research team at any time throughout the study period. A member of the research team will respond to all inquiries within one business day.

### Intervention and Control Groups

#### Baseline Assessments (Prestudy Surveys)

Both the intervention and control groups will receive access to the same prestudy surveys at T1 (baseline). The prestudy surveys will be used for the baseline assessments of participant demographics, knowledge, perceived self-efficacy, and perceived burden. Prestudy surveys will be identical for both the intervention and control groups.

#### e-Learning Content

After completion of the prestudy surveys, the intervention group will receive access to 10 selected e-learning lessons from iGeriCare (Figure 1). The control group will receive access to a single e-learning lesson on “Promoting Brain Health.” Each group will be provided access to the other group’s e-learning content at the conclusion of the study. Specific lesson titles and outlines for the intervention and control groups are displayed in Table 1.

**Figure 1 figure1:**
[figure not shown]
e-Learning content of the intervention group.

**Table 1 table1:** Study lesson titles, descriptions, and group assignment.

Title of lesson	Duration (min)	Lesson content	Group assignment
What is dementia?	10-15	Understand what cognition is and how it is impacted by dementia. Learn about the most common causes of dementia and other possible causes of dementia-like symptoms.	Intervention
The different types of dementia	20-25	Learn about the similarities and differences between Alzheimer disease, vascular, Lewy body, frontotemporal, and Parkinson disease dementias.	Intervention
Stages of dementia	20-25	Explore the 3 stages of dementia. Understand how the disease progresses and know what to expect.	Intervention
How is dementia treated?	15-20	Look into the difference between managing the symptoms of dementia and modifying the disease itself. Investigate what prescription drugs and other therapies are available.	Intervention
Safety in dementia	15-20	Become aware of the risks of wandering, driving, fire, improper use of medications, and managing personal finances. Discover strategies to reduce the possibility of harm.	Intervention
Caring for the person with dementia at home	20-25	Learn about the types of services available in your home and your community from both publicly funded sources and private companies.	Intervention
Apathy, depression, and anxiety in dementia	25-30	Learn how these psychiatric issues may affect people with dementia. Understand how to cope and discover what treatments may be available.	Intervention
Behavioral, emotional, and psychiatric symptoms in dementia	35-40	Identify the behavioral, emotional, and psychiatric signs and symptoms associated with dementia. Discover strategies and resources to help to manage responsive behaviors.	Intervention
Caregiver wellness	10-15	Understand why caregiver wellness is so important. Learn what you can do to help yourself and find support.	Intervention
Dementia: an overview	10-12	Get a quick overview of dementia in this summary that covers the highlights of all our lessons.	Intervention
Promoting brain health	25-30	Explore how diet, exercise, blood vessel health, lifestyle choices, brain and social activity, and other health conditions affect brain health.	Control

